### Study End Points

#### Primary End Points

The primary end points of the first phase for WP 1 are the proportion of different types of UTI (uncomplicated UTIs, recurrent UTIs, and pyelonephritis), the percentage of first-line antibiotics used for different types of UTI according to the national guidelines [40,41], and the percentage of inappropriate prescriptions, with the type of antibiotic of these prescriptions. The primary end points for WP 2 are the percentage hospitalization rate and the proportion of UTIs with complications (ie, pyelonephritis, sepsis, pneumonia, and COVID-19). COVID-19 infection will be determined by ICD-10 codes, tests (ie, polymerase chain reaction tests, rapid antigen tests, and others), or both.

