#### Secondary End Points

The secondary study endpoints are (1) types of UTI in women aged ≥18 years with the percentage of recurrent UTIs (defined as more than 2 UTIs in the last 6 months or more than 3 episodes in the last year); (2) types of UTI in men aged ≥18 years; (3) the percentage of urine cultures and laboratory tests ordered for the different types of UTI in both men and women; (4) the percentages of different types of antibiotics used in patients with UTIs, as well as dosage and duration of treatment; (5) the percentage of women with recurrent UTIs who were treated with suppressive therapy (ie, antibiotic treatment 3 times a week for 6 months or more) and the duration of the therapy; (6) the percentage of infectious complications, especially acute pyelonephritis and sepsis, in the 2 cohorts (ie, women with recurrent UTIs with suppressive therapy and women with recurrent UTIs without suppressive therapy but with UTIs treated punctually; (7) the percentage of pneumonia and COVID-19 infection in the 2 cohorts (ie, women with multiple antibiotic regimens for UTIs or suppressive therapy and women with UTIs treated punctually); and (8) the frequency of clinical variables of people affected by UTI who progress to acute pyelonephritis.

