### Statistical Analysis

Demographic and baseline characteristics of the participants will be reported as frequencies and percentages for categorical variables and means and standard deviation or median and interquartile range for continuous variables, as appropriate.

For WP 1, descriptive statistics will be reported for the results. For WP 2, a severity variable will be constructed that will include mortality and hospitalization, in addition to the presence of pneumonia in cases of COVID-19. Quantitative variables will be described as means and standard deviation, while categorical variables will be described as the proportion of exposed and unexposed individuals. Univariate tests will include the Student *t* test and the chi-square test, as appropriate. For the primary outcome, marginal structural models will be fitted to estimate causal effects by correcting for confounders. Inverse probability weights will be estimated as a function of propensity score using sociodemographic variables and clinical variables. The inverse probability weights will be used in the marginal structural model to estimate the risk ratio and confidence intervals for the prevalence of each outcome among individuals exposed to antibiotics versus those not exposed to antimicrobials. During the assessment of the correlation of prior antibiotic exposure with the different outcomes, patients will only be counted once and assigned to the worst outcome (with the severity of COVID-19 ranked in decreasing order as death, hospitalization, and pneumonia). The Wald test will be used to determine whether the adjusted risk ratios are significantly different from zero at a significance level of 5%.

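### No adjusted analysis is clearly assigned to the suppressive-versus-punctual comparison: the complications sit at two end point levels, and the weighted model is written for a different contrast

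*Protocol article*

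**What the plan says.** Under Primary End Points, the WP 2 items are "the percentage hospitalization rate and the proportion of UTIs with complications (ie, pyelonephritis, sepsis, pneumonia, and COVID-19". No cohorts are named there.

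Under Secondary End Points, item 6 is "the percentage of infectious complications, especially acute pyelonephritis and sepsis, in the 2 cohorts", the cohorts being women with recurrent UTI on suppressive therapy and women with recurrent UTI treated episode by episode. Item 7 is "the percentage of pneumonia and COVID-19 infection in the 2 cohorts (ie, women with multiple antibiotic regimens for UTIs or suppressive therapy", set against women whose UTIs were treated punctually.

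The Statistical Analysis section says "Univariate tests will include the Student *t* test and the chi-square test" and ties these tests to no end point. It continues: "For the primary outcome, marginal structural models will be fitted to estimate causal effects by correcting for confounders". The weights are then used "to estimate the risk ratio and confidence intervals for the prevalence of each outcome", and the groups compared are given as "among individuals exposed to antibiotics versus those not exposed to antimicrobials".

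The Objective in the Abstract and the Discussion both present the comparison of the two cohorts of women as the purpose of this part of the study.

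**The concern.** The comparison that WP 2 exists to make appears among the end points only at the secondary level. The one confounder-adjusted method in the plan is introduced for the primary level, with exposure groups that are not the two cohorts. A statistician working from this text could not tell which analysis gives the headline result for suppressive therapy.

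This matters because allocation to suppressive therapy is a clinical decision. If women who receive it differ in age, comorbidity or number of past infections, and these also raise the risk of the four complications, a crude comparison would mix the effect of treatment with the reasons for giving it. An unsettled hierarchy also leaves open, until after the data are seen, which result counts as primary.

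**Working it through.** The plan gives no figure to reproduce here, so the main check sets the sections side by side.

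**1. Overlap of end points.**
- Pyelonephritis and sepsis: WP 2 primary, and again in secondary item 6.
- Pneumonia and COVID-19: WP 2 primary, and again in secondary item 7.
- Hospitalization: WP 2 primary, not repeated in items 6 or 7.

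All four complications appear at both levels. The form differs: a proportion of UTIs at the primary level, a percentage by cohort at the secondary level.

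**2. Where the cohort contrast is stated.** Among the end points, only in secondary items 6 and 7.

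**3. Whether the two items use the same cohorts.** They do not. Item 6 separates women by suppressive therapy. Item 7 adds women with multiple antibiotic regimens to the suppressive group. A woman with recurrent UTI, several antibiotic courses and no suppressive therapy can thus belong to the comparison group in item 6 and to the more heavily treated group in item 7.

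**4. What the weighted model would estimate.**
- Narrow reading (primary outcome only): it covers the complications as listed under Primary End Points, where there are no cohorts.
- Wide reading (each outcome): it reaches items 6 and 7, but the stated contrast is still exposed against unexposed. Both cohorts in item 6 are treated with antibiotics, so that contrast does not separate them.

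Neither reading, followed literally, gives an adjusted suppressive-versus-punctual risk ratio. Correcting the contrast alone would leave the model's scope unclear; correcting the scope alone would leave the wrong groups.

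**5. Illustration of what adjustment protects against.** The inputs are assumptions, not figures from the protocol. Take a true risk ratio of 1 and one binary confounder that multiplies risk by *R*, with prevalence *p1* in the suppressive cohort and *p0* in the punctual cohort:

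unadjusted RR = (1 + *p1*(*R* − 1)) / (1 + *p0*(*R* − 1))

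- *R* = 2, *p1* = 0.4, *p0* = 0.2: 1.4 / 1.2 = 1.167
- *R* = 3, *p1* = 0.6, *p0* = 0.3: 2.2 / 1.6 = 1.375

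If the confounder were more common in the punctual cohort instead, the same inputs reversed give 1.2 / 1.4 = 0.857 and 1.6 / 2.2 = 0.727. The direction is therefore also an assumption.

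**The case against.** A reader might infer that items 6 and 7 will be tested by chi-square without adjustment. The document does not support that. No sentence assigns the univariate tests to these items, and they follow directly on the description of exposed and unexposed individuals, so they can be read as descriptive. The same section speaks of each outcome, of different outcomes and of adjusted risk ratios in the plural. Because the four complications are also primary, even the narrow scope of the model covers them as outcomes. WP 2 is described throughout as a study of antibiotic use and complications in women, so its primary end points may be meant as the cohort comparison. The Discussion also promises sensitivity analyses and further adjustment methods where appropriate, without restriction to primary end points. Finally, a condensed article may leave the matching of models to secondary end points to a fuller plan.

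Most of this stands, and it defeats the claim that the comparison will be unadjusted. It does not repair the mismatch. The article itself states the end point levels, the opening scope of the model and its exposure groups, and these do not fit together. The general promise in the Discussion names neither an end point nor a contrast. The bias figures also rest on assumed inputs: the documents do not say that women on suppressive therapy are older or sicker.

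**Conclusion.** The point holds as an inconsistency in end point level, model scope and model contrast. All four complications are listed twice, the central comparison appears only in the secondary list, and the one adjusted model is specified for groups that do not match the two cohorts. No adjusted suppressive-versus-punctual estimate is clearly assigned.

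It does not follow that the plan will produce a biased or falsely harmful result for suppressive therapy. The range of 1.17 to 1.38 shows what confounding could do if only a crude comparison were reported and the assumed prevalences and effects applied, in that direction. The actual size cannot be derived: the protocol gives a feasibility count of about 2.5 million UTIs but no cohort sizes, event rates or confounder distributions. If the cohorts are large, a bias of this order could reach significance at the 5% level, but the documents do not allow this to be quantified.

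**What to change.** - Under Primary End Points, list the cohort comparison of each complication (pyelonephritis, sepsis, pneumonia, COVID-19) once, as the WP 2 primary end point, and remove the duplicate secondary entries.
- Use one definition of the two cohorts for all four complications, since items 6 and 7 now differ. Which definition applies is for the authors to settle.
- In Statistical Analysis, state that the inverse-probability-weighted model, with those two cohorts as the exposure groups, gives the reported risk ratio for each listed complication, and that univariate tests serve only to describe the cohorts.
- If an exposed-versus-unexposed analysis is also wanted, name it separately with its own population.

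The cost is relabelling, a sentence or two in the analysis section, and running the model already planned on the listed outcomes. No new data source is needed.

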**Methods:**

The study is a population-based observational cohort study including adults with a diagnosis of UTI registered in the Information System for the Development of Research in Primary Care (in Catalan: Sistema d’informació per al desenvolupament de la investigació en atenció primària), the Minimum Basic Data Sets of Hospital Discharges and Emergency Departments (in Catalan: Conjunt mínim bàsic de dades a l’hospitalització d'aguts i d’atenció urgent), and data from the Hospital Dispensing Medicines Register (in Catalan: Medicació hospitalària de dispensació ambulatòria) of Catalonia from the period between 2012 and 2021. We will evaluate the variables obtained from the databases to analyze the proportion of different types of UTIs, the percentage of adequate antibiotic treatments prescribed or received for recurrent UTIs according to the national guidelines, and the proportion of UTIs with complications.

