## Methods

### Study Design and Population

This is a population-based observational cohort study. The inclusion period was from January 1, 2012, to December 31, 2021. The study population was patients aged ≥18 years with a diagnosis of UTI registered in SIDIAP during the study period. UTI diagnoses included the International Statistical Classification of Diseases and Related Health Problems, 10th Revision (ICD-10) codes (Table 1).

**Table 1 table1:** Health problems included in the study and their International Statistical Classification of Diseases and Related Health Problems, 10th Revision codes.

ICD-10 codes	Health problems
N10	Acute tubule-interstitial nephritis
N30	Cystitis
N30.0	Acute cystitis
N30.1	Interstitial cystitis (chronic)
N30.2	Other chronic cystitis
N30.3	Trigonitis
N30.8	Other cystitis
N30.9	Cystitis, unspecified
N34	Urethritis and urethral syndrome
N34.1	Nonspecific urethritis
N34.3	Urethral syndrome, unspecified
N39.0	Urinary tract infection, site not specified
N41	Inflammatory diseases of prostate
N41.0	Acute prostatitis
N41.1	Chronic prostatitis
N41.3	Prostatocystitis
N45	Orchitis and epididymitis
N45.0	Orchitis, epididymitis, and epididymo-orchitis with abscess
N45.9	Orchitis, epididymitis, and epididymo-orchitis without abscess

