## Discussion

We expect to find inadequate management in a high percentage of UTI cases, considering that on many occasions patients are treated with second- or third-line antibiotic therapies with a preference for the longest regimens. Likewise, the use of suppressive antibiotic therapy as a prophylaxis in cases of recurrent UTI is expected to vary in our study.

In addition, we aim to determine whether women with recurrent UTIs treated with antibiotic suppressive therapy have a higher incidence and severity of potentially serious future infections, with special attention to acute pyelonephritis, urosepsis, COVID-19, and pneumonia, in comparison to women who are treated with antibiotics only when they present with a UTI.

All the information obtained in this first phase will allow us to continue with the following WPs of the project. Furthermore, if we find the inappropriate use of antibiotics, we will work on the creation of proposals to promote the correct treatment of UTIs in our environment according to clinical guidelines [40,41]. In this way, we will promote responsible management of UTIs in PHC among health care personnel and patients. In addition, our study will provide valuable information for health care policy makers and national programs to optimize the use of antimicrobials.

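### WP 2 is specified as a risk ratio for prevalence over a ten-year rolling inclusion period, a measure that does not fit the stated aim of incidence of future infections and can be shifted by unequal time at risk

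*Protocol article*

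**What the plan says.** The Discussion (and, in near-identical terms, the conclusions of the Abstract) gives the aim of WP 2: whether women with recurrent UTI on suppressive antibiotics "have a higher incidence and severity of potentially serious future infections", compared with women treated only when they have a UTI.

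The design is a cohort: "This is a population-based observational cohort study". Entry is rolling: "The inclusion period was from January 1, 2012, to December 31, 2021". The Abstract (Methods) describes the registry data as being "of Catalonia from the period between 2012 and 2021", so the inclusion period and the data period coincide.

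The Statistical Analysis section fixes the measure. For the primary outcome, marginal structural models are to be used "to estimate the risk ratio and confidence intervals for the prevalence of each outcome among individuals exposed to antibiotics versus those not exposed to antimicrobials". Each patient enters once, at the worst outcome. On the weights it says: "Inverse probability weights will be estimated as a function of propensity score using sociodemographic variables and clinical variables".

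Under Primary End Points, the WP 2 outcomes are hospitalization and the proportion of UTIs with complications, with pneumonia and COVID-19 among the complications. Secondary end point 7 repeats the last two by cohort as "the percentage of pneumonia and COVID-19 infection in the 2 cohorts". Secondary end point 5 defines suppressive therapy by a duration of 6 months or more.

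**The concern.** A proportion that counts each woman once, over whatever time she happens to be observed, mixes two things: how fast events occur and how long she was watched. The aim concerns only the first. In a closed cohort with equal follow-up the distinction would be harmless. Here entry is spread over ten years, so a woman entering in January 2012 may contribute up to ten years and one entering in December 2021 almost nothing.

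If the two WP 2 cohorts differ in calendar time of entry, mortality or deregistration, the ratio of proportions departs from 1 even when the underlying rates are equal. Weighting on patient characteristics balances those characteristics; it does not equalise observation time. With about 2.5 million UTIs in the feasibility count, precision may well be high enough for a modest artefact to pass the 5% Wald test and be read as an effect of suppressive therapy.

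The exposure definition adds to this. A woman must survive and remain observed through at least 6 months of therapy to be classed as exposed, and no such condition applies to the comparison cohort. Equal time at risk is therefore unlikely.

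**Working it through.** The article gives no figure on this point to reproduce. The check has two parts: calendar arithmetic from the stated dates, and illustrations under a true rate ratio of 1.

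**Calendar arithmetic**
- Inclusion period (Study Design and Population): 1 January 2012 to 31 December 2021 = 3653 days = 10.0 years.
- If observation ends with the data period, follow-up ranges from 0 to 10 years. Entry uniform over the decade would give a mean of 5.0 years.
- COVID-19 onset is not in the article. Assuming 1 January to 1 March 2020, time to 31 December 2021 is 2.00 to 1.84 years, or 20% to 18% of the ten years.

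**Model for the illustrations.** Cumulative proportion = 1 − exp(−rate × time), with the same rate in both cohorts. Assumed rates: 0.005, 0.01 and 0.05 per person-year. Rates, follow-up times and entry patterns are all assumptions.

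*Different mean follow-up, treated as fixed times*
- 4 v 5 years, rate 0.05: (1 − e^−0.20)/(1 − e^−0.25) = 0.181/0.221 = 0.82. Rate 0.005: 0.0198/0.0247 = 0.80.
- 6 v 4 years, rate 0.05: (1 − e^−0.30)/(1 − e^−0.20) = 0.259/0.181 = 1.43. Rate 0.005: 0.0296/0.0198 = 1.49.

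*The 6-month requirement, entry uniform over ten years*
- Exposed follow-up starts 6 months later, and women with under 6 months left stay in the denominator with no time at risk: 0.90 to 0.91. At low rates this is the ratio of mean times, (9.5²/20)/5 = 4.51/5 = 0.90.
- The same, but those women are dropped: 4.75/5 = 0.95 at low rates, 0.96 at rate 0.05.
- Events counted from entry, with exposed women required to have at least 6 months: 5.25/5 = 1.05.

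So the direction depends on how time is counted, which the article does not say.

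*Pneumonia and COVID-19 under the same entry shift* (one cohort entering 2017 to 2021, the other 2012 to 2021; COVID-19 time taken as the last 2 years)
- Pneumonia: 0.50 to 0.54.
- COVID-19: 0.89.

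*COVID-19 with loss before 2020*
- If 10% of one cohort and 20% to 30% of the other leave observation before 2020 but stay in the denominator: 0.90/0.80 = 1.13 to 0.90/0.70 = 1.29.

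**After the change.** With the same fixed window in both cohorts, or a rate ratio per unit of person-time, equal rates give 1.00.

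**The case against.** The strongest reply is that this is a condensed article. Index date, censoring and observation window are commonly left to the full protocol, the SAP or the variable appendix, none of which is shown, and their absence is no error. That is right, and the point does not rest on it. It rests on the measure that the article does fix: a ratio for prevalence, counted once per patient, set against an aim of incidence of future events.

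Three further objections stand in part:
- The classes of weighting variables are broad and not a closed list, so index year is not excluded. It is only not named. Putting it in the propensity score would balance entry year but would not deal with differential death or deregistration. The sensitivity analyses promised in the Discussion address confounding and do not mention follow-up.
- The unit is unclear. The primary end point speaks of a proportion of UTIs, while the analysis counts each patient once. The illustrations take the per-patient reading.
- The analysis text speaks of prior antibiotic exposure, and the Introduction cites a SIDIAP study with a 2-year look-back. A look-back design is compatible with the text but is not stated.

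A reader might infer that COVID-19 is the worst-affected outcome because it could occur only in the last fifth of the period. The documents do not support this. Women who entered before 2020 and stayed under observation share the same COVID-19 window. Under the same entry shift COVID-19 moves to 0.89 and pneumonia to 0.50 to 0.54. A short disease period is not in itself a bias. Nor does it follow that the last 6 months of the data distort the estimate by their share of the pandemic period: that is a share of calendar time, not an effect on the ratio.

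**Conclusion.** The point holds as a mismatch between the stated measure and the stated aim. Followed as written, the WP 2 primary comparison sets cumulative proportions over unequal observed time against each other, and nothing stated about the weights corrects for that.

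Its size is conditional. The 0 to 10 year range is inferred from the inclusion and data periods. Bias arises only if time at risk differs between cohorts, and the article gives no data on whether or how far it does. Under a true rate ratio of 1 and assumed rates, the ratio is 0.80 to 0.82 for mean follow-up of 4 v 5 years and 1.43 to 1.49 for 6 v 4 years. It is about 0.90 if exposed follow-up starts 6 months later, or about 0.95 if women with too little time left are dropped. These show how sensitive the measure is; they do not predict the result.

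The distortion is likely larger for pneumonia, pyelonephritis, sepsis and hospitalization than for COVID-19, where it comes from women who leave observation before the pandemic or enter during it. It would be too strong to say that the WP 2 result will be biased, or in which direction.

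**What to change.** In the Statistical Analysis section, replace the prevalence ratio with weighted risks and risk ratios at a common fixed horizon (for example 12 months) from a defined index date. A time-to-event or person-time measure would serve equally. Specify:
- the index date for each cohort, set so that the 6-month exposure requirement does not give one cohort a different start of follow-up;
- censoring at deregistration and at 31 December 2021;
- death as censoring or as a competing event for the non-fatal outcomes, bearing in mind that it is itself part of the severity outcome;
- index year in the propensity score.

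For COVID-19, restrict the comparison to women alive and registered at a stated pandemic start date, classify antibiotic exposure in a fixed look-back ending before that date, and follow to 31 December 2021. Word the WP 2 end points to match.

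The cost is wording and some programming on dated, linked records; the team should confirm that deregistration dates are in the extract, because the article's variable list does not name them. The COVID-19 analysis will include fewer women.

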**Objective:**

This paper presents the protocol for the first phase of the Urinary Tract Infections in Catalonia (Infeccions del tracte urinari a Catalunya) project. We aim to examine the epidemiology of the different types of UTIs in Catalonia (an autonomous community in Spain) and their diagnostic and therapeutic management by health professionals. Furthermore, we aim to evaluate the correlation between types and total consumption of antibiotics for recurrent UTIs in 2 cohorts of women with the presence and severity of infectious complications of urological origin, especially pyelonephritis and sepsis, and 2 potentially serious infections: pneumonia and COVID-19.

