**Conclusions:**

We expect to find a high percentage of UTI cases with inadequate management according to the national guidelines, considering that on many occasions UTIs are treated with second- or third-line antibiotic therapies with a preference for the longest regimens. Furthermore, the use of antibiotic suppressive therapies, or prophylaxis, in recurrent UTIs will likely be highly variable. Moreover, we aim to determine whether women with recurrent UTIs treated with antibiotic suppressive therapies have a higher incidence and severity of potentially serious future infections, with special attention to acute pyelonephritis, urosepsis, COVID-19, and pneumonia, compared to women who receive antibiotic treatment after they present with a UTI. This is an observational study of data from administrative databases that will not allow causality analysis. The limitations of the study will be handled according to the appropriate statistical methods.

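### Secondary end points 6 and 7 give the two cohorts of women different definitions, and the arms of end point 7 overlap

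*Protocol article*

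**What the plan says.** Secondary End Points lists two items that both refer to the same two cohorts, but the groups spelled out differ.

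- End point 6, for infectious complications (chiefly pyelonephritis and sepsis): "women with recurrent UTIs with suppressive therapy and women with recurrent UTIs without suppressive therapy but with UTIs treated punctually".
- End point 7, for pneumonia and COVID-19: "women with multiple antibiotic regimens for UTIs or suppressive therapy and women with UTIs treated punctually".

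The same section gives the two definitions that bear on membership. Recurrent UTI is "defined as more than 2 UTIs in the last 6 months or more than 3 episodes in the last year", and suppressive therapy is "antibiotic treatment 3 times a week for 6 months or more".

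Elsewhere the article describes a single contrast. The Objective in the Abstract relates "types and total consumption of antibiotics for recurrent UTIs in 2 cohorts of women" to all four outcomes. The Discussion asks whether "women with recurrent UTIs treated with antibiotic suppressive therapy have a higher incidence and severity of potentially serious future infections", names pyelonephritis, urosepsis, COVID-19 and pneumonia together, and sets this "in comparison to women who are treated with antibiotics only when they present with a UTI". The Conclusions in the Abstract say the same, "compared to women who receive antibiotic treatment after they present with a UTI".

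Statistical Analysis states the modelled contrast in a third way: people with antibiotic exposure against people without it.

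**The concern.** A reader who takes the aim from the Abstract or the Discussion expects one exposure contrast across four outcomes. Followed as written, end points 6 and 7 would give two different contrasts under one label. A difference between the pyelonephritis and sepsis results and the pneumonia and COVID-19 results could then arise only because women were classified differently.

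End point 7 also cannot be programmed as it stands, because some women satisfy both of its cohort descriptions.

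The problem may reach beyond the secondary end points. Primary End Points for WP 2 names the same four complications, and items 6 and 7 are where the article spells out membership of the two cohorts.

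**Working it through.** No sample size, power or event figure bears on this point, so there is no figure of the plan's to reproduce. The check is to place defined types of women under each end point as worded.

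**Step 1: courses implied by recurrence.** More than 2 UTIs in 6 months means at least 3. More than 3 in a year means at least 4. With one course per episode, a woman who meets the definition has at least 3 courses in 6 months or at least 4 in a year.

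**Step 2: classification.**

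| Woman | End point 6 | End point 7 |
|---|---|---|
| Recurrent UTI, suppressive therapy | First cohort | First cohort |
| Recurrent UTI, no suppressive therapy, treated per episode | Second cohort | First cohort if her courses count as *multiple*; also fits the second |
| UTI treated once, not recurrent | Neither | Second cohort if the wording is literal; neither if *recurrent* is implied |

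The second row is the core of the point. The woman is unambiguously a comparator in 6. In 7 she can fall in either arm or in both.

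**Step 3: does a threshold for *multiple* remove the problem?** The article sets none. The Introduction mentions more than 5 regimens in 2 years, but as a finding of an earlier study and not as a rule for this one. Suppose that cut applied. A woman with only 3 or 4 courses in the 2 years would stay a comparator in 7. A woman with 4 treated episodes in each of 2 years has 4 + 4 = 8 courses, which exceeds 5, so she would change sides. A threshold alters how many women switch. It does not stop the switching, and it does not make the arms exclusive unless the second cohort is also defined as lying below it.

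**Step 4: does the analysis section settle it?** No. Women treated per episode have received antibiotics, so neither cohort of end point 6 is unexposed. The same holds for the punctually treated women in end point 7. The exposed-versus-unexposed contrast in Statistical Analysis matches neither pair.

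**The case against.** Four objections deserve an answer.

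**The broader exposure may be deliberate.** The Objective speaks of total antibiotic consumption, and the Introduction cites a link between cumulative antibiotic use and COVID-19 severity. A cumulative-exposure contrast for pneumonia and COVID-19 would be reasonable. This stands as a reason to keep such an analysis. It does not justify giving it the label used in end point 6, nor presenting it as the comparison promised in the Discussion, and the overlap remains.

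**The missing word *recurrent* may be shorthand.** Item 7 follows item 6 directly, the Objective ties all outcomes to recurrent UTIs, and the Abstract and Discussion also describe the comparator without repeating the word. This is a fair reading. Confounding by recurrence is therefore conditional on the literal reading. Shorthand does not explain the added repeated-course criterion.

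**Her exposed status in 7 is not certain.** The recurrence definition counts episodes, not courses, and the Discussion says diagnoses and treatments are not linked, so courses must be matched to episodes by date. This is correct. The supportable statement is that she can be classed as exposed, not that the two end points always classify her in opposite ways.

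**The detail may be in a fuller document.** An article may leave thresholds to an analysis plan. The fault here is not missing detail but two incompatible cohort descriptions under one name in current text.

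**Conclusion.** The inconsistency is real and should be resolved before the cohorts are drawn. It rests only on the wording of end points 6 and 7, set beside the single contrast in the Abstract and Discussion. No text in the article reconciles them.

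A reader might infer more than the documents support, in two ways.

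- **That per-episode women are the largest group, or that the remaining comparators in 7 are mostly women without recurrence.** Sample Size gives only a count of about 2.5 million UTIs and no cohort sizes, so neither can be said.
- **That a suppressive-therapy effect would be diluted by a known amount.** Assume, for illustration, that 10% of women with recurrent UTIs take suppressive therapy with a true risk ratio of 1.5.
  - If all other women with recurrent UTIs enter the exposed arm at a risk ratio of 1.0, the arm averages 0.10 × 1.5 + 0.90 × 1.0 = 1.05.
  - If repeated courses themselves carry 1.3, the result is 0.10 × 1.5 + 0.90 × 1.3 = 1.32.
  - If only 20% of the non-suppressed women count as *multiple*, at a risk ratio of 1.0, the suppressive share is 0.10 / (0.10 + 0.20 × 0.90) = 0.10 / 0.28 = 36%, and the average is 0.36 × 1.5 + 0.64 × 1.0 = 1.18.

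Every input in these three results is assumed, and a risk ratio of 1.0 for repeated courses goes against the study's own rationale in the Introduction. The spread from 1.05 to 1.32 shows that no size can be attached to the point.

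**What to change.** Reconcile the Objective and Conclusions in the Abstract, Secondary End Points 6 and 7, Statistical Analysis and the Discussion.

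1. For the comparison stated in the Abstract and Discussion, use one pair of mutually exclusive cohorts within women meeting the recurrent-UTI definition: suppressive therapy against per-episode treatment. Apply it to all four outcomes.
2. Analyse the number of antibiotic courses as a separate cumulative-exposure contrast under its own name. State what *multiple* and *punctually* mean, state whether the population is restricted to recurrent UTI, and make the groups non-overlapping.
3. In Statistical Analysis, replace the exposed-versus-unexposed wording with the contrast or contrasts so named.

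If the sponsor wants the broader exposure for pneumonia and COVID-19, two contrasts that are explicitly named, each with exclusive groups, would also remove the contradiction. The Abstract and Discussion would then have to say that the outcomes are compared on different exposures.

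The cost is a change of wording and one extra analysis. Prescriptions and pharmacy invoice data are already listed under Variables, and the Discussion already plans to use prescription and diagnosis dates.
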